#### 12.1.2 Secondary outcome measures

- Proportion of patients with a reduction in the peripheral blood JAK2-V617F, CALR 5bp insertion (exon 9), or CALR 52bp deletion (exon 9) mutant allele burden of  $\geq 50\%$  at 12 weeks
- Toxicity measured as the number of grade 3 and 4 adverse events reported.
- The number of thrombotic events of any grade reported and validated.
- Haematological response, assessed at weeks 12 and 24, for patients who enter the study in response (CR or PR). Haematological response is defined according to 2009 ELN criteria for ET/PV patients and no evidence of disease progression for MF patients according to IWG-MRT response criteria (for criteria see Appendices 5 & 6).
- Proportion of patients in each response category according to IWG-MRT response criteria for MF patients and 2013 ELN response criteria for ET/PV patients at 24 weeks of treatment.
- Proportion of patients showing an improvement in response category at 24 weeks compared to baseline according to 2009 ELN criteria for ET/PV patients [1] and according to IWG-MRT response criteria [2] for MF patients. Patients who are in a higher category at week 24 compared to baseline will be classed a success. Patients who enter the trial in CR and who maintain a CR will also be classed as a success in this outcome.

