## 1.2 Trial Rationale

### 1.2.1 Justification for patient population

This trial will be open to all patients with MPN who have a measureable disease burden (defined by quantifiable abnormal clone of  $\geq 20\%$  mutated JAK2-V617F, CALR 5bp insertion (exon 9) or CALR 52bp deletion (exon 9)).

The eligibility criteria have also been carefully considered to take into account the well-established safety profile of tamoxifen and the trial is therefore open only to males and post-menopausal women.

Patients with a prior thrombosis will also be excluded as both tamoxifen and MPN are associated with a higher risk of thrombosis. To try and ensure patients have stable blood counts whilst on trial, and again minimise the risk of thrombosis, patients will also be able to continue with existing therapy for their MPN such as hydroxycarbamide, venesection, and aspirin. However, patients will not be able to continue/receive concomitant treatment with therapies that lower the allele burden such as interferon alpha) as this would prevent accurate assessment of the primary outcome. JAK inhibitors, such as ruxolitinib, will be allowed if taken continuously for  $\geq 6$  months prior to registration, as any changes in allele burden are expected to occur early during treatment.

In addition, only patients whose disease is currently well controlled on standard therapies will be eligible which will further minimise the risk of thrombosis.

Another well described side effect of tamoxifen is women experiencing symptoms of premature menopause and uterine changes. This study will therefore only include post-menopausal women.

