### 4.2 Exclusion Criteria

- Leukaemic transformation ( $>20\%$  blasts in blood, marrow or extramedullary site).
- Accelerated phase of disease as indicated by  $\geq 10\%$  blasts in the peripheral blood
- Treatment of ET, PV or MF with Interferon alpha or other investigational agents for their MPN within 6 months prior to trial entry. JAK inhibitors, such as ruxolitinib, are allowed if taken continuously for  $\geq 6$  months prior to registration (dose changes during that period will be allowed)
- Any of the following previous thrombotic events at any time:
  - Portal or other splanchnic venous thrombosis
  - Vascular access complication
  - Ischemia cerebrovascular
  - Stroke
  - Transient Ischaemic attack
  - Superficial thrombophlebitis
  - Venous Thromboembolic events including pulmonary embolism (PE) and deep vein thrombosis (DVT)
  - Peripheral vascular ischemia
  - Visceral arterial ischemia
  - Acute coronary syndrome
  - Myocardial infarction

- Previous malignancy within 5 years with the exception of adequately treated cervical carcinoma in situ or localized non-melanoma skin cancer
- Previous endometrial cancer, hyperplasia or polyps
- Prior treatment with hematopoietic stem cell transplantation
- Patients who do not carry JAK-2V617F, CALR 5bp insertion (exon 9) or CALR 52bp deletion (exon 9) mutations, or whose allele burden is <20% at study entry (**assessed via central review**)
- Female patients receiving hormone replacement therapy
- Hypertriglyceridemia > grade 1
- Any serious underlying medical condition (at the judgment of the Investigator), which could impair the ability of the patient to participate in the trial (e.g. liver disease, active autoimmune disease, uncontrolled diabetes, uncontrolled infection (HIV, Hepatitis B and C), known genetic defect (apart from MPN) relating to venous thromboembolic events, or psychiatric disorder precluding understanding of trial information)
- Known hypersensitivity to tamoxifen or hypersensitivity to any other component of tamoxifen
- Concomitant drugs contraindicated for use with the trial drug according to the Summary of Product Characteristics (Appendix 8)
- Known planned scheduled elective surgery during study with the exception of dental and low risk eye surgery (e.g. cataracts)

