## 7. TREATMENT DETAILS

### 7.1 Trial Treatment

Tamoxifen is considered an investigational medicinal product (IMP) for the purposes of the trial from the point of dispensing.

Sites are to use tamoxifen from standard hospital stock. No free or discounted product is offered as part of the trial.

Any brand of tamoxifen may be used provided it is in tablet form and administered orally.

Medication labels in English will be provided in the Pharmacy File. These must be added at the point of dispensing and the local information and patient trial number added.

Patients should be given enough tamoxifen to last until their next scheduled visit but the schedule for prescribing is at local site discretion (e.g. can be prescribed 4 weekly initially, rather than 2 weekly).

Patients will receive 20mg once daily. Patients should start trial treatment following registration but this must be within 6 weeks of the assessment of allele burden and continue daily for 24 weeks. At this point, further treatment may be prescribed if the patient is receiving benefit (at the discretion of the treating Investigator).

As guidance, treatment continuation will be encouraged but not mandated for patients who do not experience persistent side effects greater than grade 1 or thrombotic events of any grade and that fulfil one or more of the following criteria at 24 weeks:

- $\geq 25\%$  reduction in allele burden compared to baseline
- Improvement of haematological response compared to baseline without changes in cytoreductive therapy dose according to 2009 ELN criteria for ET/PV patients and to IWG-MRT response criteria for MF patients
- A decrease in requirement for cytoreduction without deterioration of haematological response compared to baseline according to 2009 ELN criteria for ET/PV patients and to IWG-MRT response criteria for MF patients

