### 12.2.3 Exploratory outcome measure

All exploratory outcomes will be analysed in a descriptive manner on an intention to treat basis with no formal hypothesis testing taking place.

- Change in allele burden at 12 and 24 weeks compared to baseline will be obtained following analysis of peripheral blood at University of Cambridge and will be presented as the median change from baseline at each time point with the interquartile ranges.
- Proportion of patients showing a decrease in requirement for cytoreduction therapy at 24 weeks compared to baseline will be presented as the number and percentage of patients who have a decrease in treatment dose. Patients who die or are lost to follow up prior to week 24 will be classed as non-responders.
- Proportion of patients showing a decrease in allele burden of  $\geq 50\%$  at 36 and 48 weeks compared to baseline will also be obtained following analysis of peripheral blood at University of Cambridge. Counts and percentages of patients who have achieved the reduction at 36 and 48 weeks will be presented. This will only be presented for patients who remain on treatment post week 24 and are assessed at week 36 and week 48, respectively.
- 
- Duration of reduction in the peripheral blood JAK2-V617F, CALR 5bp insertion (exon 9), or CALR 52bp deletion (exon 9) mutant allele burden, defined as time between visits from first

observed reduction of  $\geq 50\%$  until the visit at which reduction from baseline becomes  $< 25\%$  or the last visit before the patient dies, will be tabulated.

- Expression (RNAseq), DNA-protein interaction (ChIPSeq) and methylation studies will be analysed and presented by the University of Cambridge.

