### 12.6 Power Calculations

A single stage A'herns design is used to give evidence of activity for the treatment. It is anticipated that no patients on the current treatment will achieve a reduction of  $\geq 50\%$  in allele burden. Given this, if 10% of the patients in this trial were to achieve the required reduction then the treatment would warrant further investigation in a randomised trial. If just 2% of the patients in the trial were to achieve the required level of reduction then the treatment would not be deemed to show any activity that would warrant further investigation. Based on these levels of acceptability and given a one sided alpha of 0.1 and power of 80%, 42 patients would be required for the study. If 3 or more of the recruited patients were to achieve a reduction in allele burden of  $\geq 50\%$  then it can be concluded that the treatment shows a signal of activity and the treatment warrants further investigation in a randomised trial. Patients who die or are lost to follow up prior to the response time point of 24 weeks will be classed as non-responders.

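### Sections 12.1.2 and 12.2.3 drop the background-therapy conditions that section 7.1 attaches to haematological benefit, so a cytoreductive dose increase, or a dose cut with lost response, can count as a success

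*Combined protocol and SAP*

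**What the plan says.** **Category improvement (secondary; 2.2, 12.1.2, 12.2.2).** "Patients who are in a higher category at week 24 compared to baseline will be classed a success". Patients who enter in CR and keep it are also successes. The result is one number and percentage. No condition concerns background MPN drugs.

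**Requirement for cytoreduction (exploratory; 12.1.3, 12.2.3).** The result "will be presented as the number and percentage of patients who have a decrease in treatment dose". Neither the reason for the decrease nor the response afterwards is considered.

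**Continuation guidance (7.1).** Two of the benefits that support treatment beyond week 24 carry conditions:
- "Improvement of haematological response compared to baseline without changes in cytoreductive therapy dose according to 2009 ELN criteria"
- "A decrease in requirement for cytoreduction without deterioration of haematological response compared to baseline"

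**Background drugs.** Section 7.6 keeps patients on cytoreductive therapy and does not say that doses are held fixed. Section 4.2 accepts JAK inhibitors taken continuously for at least 6 "months prior to registration (dose changes during that period will be allowed"). Section 1.2.1 excludes concomitant drugs that lower allele burden, with interferon alpha as the example, "as this would prevent accurate assessment of the primary outcome".

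**Primary rule (12.2.1, 12.6).** At least 3 responders in 42 is the signal of activity. The null rate is 2% and the target 10%. "It is anticipated that no patients on the current treatment will achieve a reduction of" 50% or more. Only death and loss to follow-up are assigned an outcome (non-response).

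**The concern.** The authors saw the problem when they wrote section 7.1: counts can improve because another drug was increased, and a dose can fall without the patient needing less treatment. The outcome definitions use the same two ideas without those safeguards.

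In a randomised trial, background changes would occur in both arms and the comparison would absorb much of their effect. Here there is one arm, so a change driven by hydroxycarbamide, anagrelide or a JAK inhibitor enters the tamoxifen column and cannot be separated afterwards unless it was defined and tabulated. Pooling maintained CR with improvement adds patients already in CR on their existing therapy.

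What is at stake is mainly the reading of one secondary and one exploratory outcome, which would inform the case for a randomised trial. There is a smaller stake in the primary decision, because a threshold of three responders leaves little room for one or two that tamoxifen did not cause.

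**Working it through.** **1. The definitions side by side**

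| Idea | Section 7.1 (continuation) | Section 12 (outcome) |
|---|---|---|
| Better haematological response | Cytoreductive dose unchanged | Higher category at week 24; no condition |
| Less cytoreduction | Response not worse than baseline | Any decrease in dose |
| CR kept from entry | Not listed as a benefit | Counted as a success |

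**2. Can a dose increase produce a success under the plan's own criteria?** Section 4.1 admits ET patients with platelets up to 600 × 10⁹/L and WBC up to 25 × 10⁹/L. Appendix 5 calls ET platelets of 600 or less a PR. CR needs platelets of 400 or less, WBC of 10 or less and normal spleen size. Every ET patient who meets the entry platelet limit is therefore in at least PR, and the step to CR turns largely on counts that cytoreduction is given to control. A dose increase that achieves the step is a success in 12.1.2 and would not qualify under 7.1. That doses may move on trial is presupposed by the cytoreduction outcome itself.

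**3. Size for the secondary and exploratory outcomes.** On the intention-to-treat denominator, one patient is 1/42 = 2.4 percentage points. The documents do not say how many such patients to expect.

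**4. The primary rule.** Inputs from 12.6: n = 42, threshold r = 3, p0 = 0.02, p1 = 0.10, one-sided alpha 0.10, power 80%.

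P(X ≥ 3) = 1 − (1−p)⁴² − 42p(1−p)⁴¹ − 861p²(1−p)⁴⁰

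- p = 0.02: 1 − 0.4281 − 0.3669 − 0.1535 = 0.0515, the exact type I error.
- p = 0.10: 1 − 0.0120 − 0.0559 − 0.1273 = 0.805, the power.

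The stated design reproduces: 42 with r = 3 is the smallest design meeting both limits.

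**5. Sensitivity to background-driven responders.** Assume tamoxifen is inactive, k patients are certain to respond because of another drug, and the rest respond at 2%:

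- k = 1: P(at least 2 of 41) = 1 − 0.98⁴¹ − 41(0.02)(0.98⁴⁰) = 1 − 0.4368 − 0.3655 = 0.198
- k = 2: P(at least 1 of 40) = 1 − 0.98⁴⁰ = 0.554

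If the rest respond at 0%, as 12.6 anticipates, one or two such responders cannot reach three.

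**6. A less extreme version.** Suppose 10 of the 42 have a JAK-inhibitor change that gives each a chance q of a 50% fall, and the other 32 respond at rate p. Both q and the 10 are assumptions. Adding Binomial(10, q) and Binomial(32, p):

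| q | p | P(≥ 3), tamoxifen inactive |
|---|---|---|
| 10% | 2% | 0.223 |
| 5% | 2% | 0.105 |
| 10% | 0% | 0.070 |

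The answer runs from inside the 0.10 limit to more than twice it, according to inputs the documents do not supply.

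**7. What reclassifying responders in the primary analysis would cost.** If a share d of true responders were set to non-response, the response rate under the target becomes 0.10(1 − d). Power is 0.741 for d = 10% and 0.664 for d = 20%, against 0.805 for d = 0.

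**The case against.** **Section 7.1 is guidance on continuing treatment, not an outcome definition.** True, so the two need not match word for word. But the reasons for the conditions apply at least as strongly to an outcome in an uncontrolled trial, and section 12 gives no reason for leaving them out.

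**The affected outcomes are descriptive.** This stands. Sections 12.2.2 and 12.2.3 disclaim formal hypothesis testing, and neither outcome enters the 3-of-42 rule. It limits the weight of the point without answering it.

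**Counting maintained CR is explicit, and haematological response in patients entering in CR or PR is tabulated separately at weeks 12 and 24.** Also true. The remaining complaint is only that a single combined percentage will be read as improvement.

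**A cut made for toxicity is not in conflict with section 7.1.** Correct. Section 7.1 asks only that response has not deteriorated, so the reason for a cut should be tabulated, not used to exclude the patient.

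**The primary outcome is protected elsewhere.** A reader might infer that a JAK inhibitor newly started on trial goes unaddressed because section 7.7 names only interferon among MPN drugs. The documents do not support this: section 1.2.1 excludes allele-lowering therapies generally and admits JAK inhibitors only after at least 6 months of continuous use. A reader might also take the outcome definitions to be the only safeguard. They are not: sections 4.1 and 4.2 require no new MPN agent for 6 months, stable counts and venesection (PV/ET) or no progression (MF), and no recent interferon or investigational agents. The 2% null also sits above the 0% that 12.6 anticipates. What remains open is a dose change of an established JAK inhibitor, before registration or on trial, and the absence of any analysis rule should a drug be started despite these restrictions.

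**Conclusion.** The point holds for the category-improvement and cytoreduction outcomes. Section 12 omits two conditions that section 7.1 states, and following it literally credits tamoxifen with effects of other drugs. Each affected patient moves the proportion by 2.4 percentage points. How many there will be is unknown.

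For the primary outcome the conclusion is narrower. No stated figure is wrong: the design gives an exact type I error of 0.052 and power of 0.805. The threshold is sensitive to few cases (0.198 with one certain background-driven responder and the rest at 2%), and nothing planned would show whether such a case contributed.

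A reader might infer that the false-positive rate is really about 0.22. The documents do not support that: it needs 10 patients with a relevant change, a 10% response in each (the rate the plan sets for active tamoxifen) and 2% in everyone else. Changing one input gives 0.105 or 0.070. Section 1.1 also describes access to ruxolitinib as very limited, especially in PV, the group with the largest recruitment minimum. Nor do the documents support making every patient with a background change a primary non-responder: it departs from the plain intention-to-treat count and lowers power, to 74.1% if 10% of true responders are affected.

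This should be corrected, but it does not invalidate the design.

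**What to change.** 1. **Sections 2.2, 12.1.2 and 12.2.2.** Count improvement as a higher category at week 24 with no new MPN agent and no increase in cytoreductive dose since baseline. A patient who improves on a lower dose still counts, since the background drug does not explain the gain. Report improvement among patients not in CR at entry separately from maintained CR.
2. **Sections 12.1.3 and 12.2.3.** Count a decrease in cytoreduction only if haematological response has not deteriorated from baseline. Tabulate the reason for the decrease where it is recorded.
3. **Section 12.2.1.** Keep the intention-to-treat 3-of-42 rule. Prespecify a sensitivity count that lists responders with a JAK-inhibitor dose change in the 6 months before registration, or with any MPN-drug start or JAK-inhibitor increase on trial. Repeat the count of responders without them, keeping 42 as the denominator.

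These change only what is counted and reported, not how patients are treated.

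**Cost.** The secondary and exploratory success proportions may be slightly lower. Section 12 is protocol text, and past outcome updates were logged within substantial amendments, so this is a protocol wording change. Concomitant medication is already recorded continuously (section 9.1), but no form is shown to capture the reason for a dose change, so one eCRF field may be needed; section 9.1 lets the Trials Office amend forms without a protocol amendment. Sample size, threshold and primary power are unchanged.

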#### 12.1.3 Exploratory outcome measure

- Change in JAK2-V617F, CALR 5bp insertion (exon 9), or CALR 52bp deletion (exon 9) allele burden between weeks 12, 24 and baseline.
- Proportion of patients showing a decrease in requirement for cytoreduction at 24 weeks compared to baseline
- Proportion of patients showing a decrease in the peripheral blood JAK2-V617F, CALR 5bp insertion (exon 9), or CALR 52bp deletion (exon 9) mutant allele burden of  $\geq 50\%$  at 36 and 48 weeks compared to baseline

- Duration of reduction in the peripheral blood JAK2-V617F, CALR 5bp insertion (exon 9), or CALR 52bp deletion (exon 9) mutant allele burden, defined as time from first observed reduction of  $\geq 50\%$  until reduction from baseline becomes  $< 25\%$  or patient death.
- The expression (RNAseq), DNA-protein interaction (CHIP-Seq) and methylation studies focused on oestrogen receptor signalling in haematopoietic progenitors will be performed in the lab of [name] at the University of Cambridge following the collection of peripheral blood (baseline and 24 weeks, plus 36 weeks and 48 weeks if patients continue treatment beyond 24 weeks as applicable) and bone marrow aspirate samples (24 weeks only).

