### 12.2.2 Secondary outcome measures

All secondary outcomes will be analysed in a descriptive manner on an intention to treat basis with no formal hypothesis testing taking place.

- The reduction in the allele burden of  $\geq 50\%$  at 12 weeks will also be obtained following analysis of peripheral blood at University of Cambridge. Counts and percentages of patients who have achieved each level of reduction at 12 weeks will be presented. Patients who die or are lost to follow up prior to 12 weeks will be classed as non-responders.
- The total number of grade 3 and 4 adverse events reported will be presented as well as the number of patients who have experienced one or more of these events.
- The total number of thrombotic events (of all grades) will be reported as well as the number of patients who have experienced one or more of these events.
- Haematological response at weeks 12 and 24 will be tabulated and compared using a  $\chi^2$  test or Fisher's exact test if the first is not considered appropriate.
- Proportion of patients in each response category at 24 weeks of treatment will be presented as the number and percentage of patients in each category.
- Proportion of patients showing an improvement in response category at 24 weeks will be presented as the number and percentage of patients who have shown an improvement (or maintained a CR).

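### Two non-primary outcomes, improved response category and reduced cytoreduction, do not separate a tamoxifen effect from changes in background cytoreductive dose

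*Combined protocol and SAP*

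**What the plan says.** **Secondary outcome.** Sections 2.2 and 12.1.2 define improvement in response category at week 24 using the 2009 ELN criteria for ET/PV and the IWG-MRT criteria for MF: "Patients who are in a higher category at week 24 compared to baseline will be classed a success". They add a second route: "Patients who enter the trial in CR and who maintain a CR will also be classed as a success in this outcome". Section 12.2.2 reports the number and percentage. None of the three mentions cytoreductive dose.

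**Exploratory outcome.** Section 12.1.3 lists "Proportion of patients showing a decrease in requirement for cytoreduction at 24 weeks compared to baseline". Section 12.2.3 says that this "will be presented as the number and percentage of patients who have a decrease in treatment dose". The only non-responders it names are patients who die or are lost to follow-up before week 24.

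**Continuation guidance.** Section 7.1 lists the findings at 24 weeks that favour continuing tamoxifen. Two of them are "Improvement of haematological response compared to baseline without changes in cytoreductive therapy dose" and "A decrease in requirement for cytoreduction without deterioration of haematological response compared to baseline", judged by the same 2009 ELN and IWG-MRT criteria.

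**Background treatment.** Section 4.1 requires patients to be receiving cytoreductive therapy, and section 7.6 says they should continue it. The bar on new MPN agents in section 4.1 covers the 6 months before registration. Section 7.7 restricts interferon alpha and drugs that interact with tamoxifen. No section fixes the cytoreductive dose over the 24 weeks or says how a change is analysed.

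**The concern.** Cytoreductive drugs act on the quantities that define the response category. Section 1.1 says hydroxycarbamide is added to bring the platelet count down. ET patients must have kept platelets at or below 600 × 10⁹/L for 3 months to enter, which already meets the 2009 ELN definition of partial response (PR). Their only upward step is from PR to CR, which turns on platelets ≤400, white cells ≤10 and a normal spleen (Appendix 5). A higher background dose could produce that step without tamoxifen.

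The other outcome has the reverse problem. Section 12.2.3 turns a reduced requirement into a reduced dose. A dose cut because of cytopenia, followed by loss of response, shows no reduced requirement, yet it is counted.

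In a single-arm trial no comparison group absorbs such changes. A reader of the two percentages could not tell tamoxifen benefit from adjustment of the background drug.

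**Working it through.** **1. The trial's main design figure.** Section 12.6 gives N = 42 and a threshold of 3 responders, with rates of 2% and 10%, one-sided alpha 0.1 and power 80%. From the binomial distribution, P(X ≥ 3) = 1 − P(0) − P(1) − P(2):
- at 2%: 1 − 0.4281 − 0.3669 − 0.1535 = 0.0515
- at 10%: 1 − 0.0120 − 0.0559 − 0.1273 = 0.8049 (from unrounded terms)

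A search over sample size and threshold confirms 42 as the smallest size that meets both limits. The figure reproduces. It concerns allele burden only, so this point does not touch it.

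**2. Cases side by side.**

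| Patient at week 24 | Counted by the outcome? | Meets the matching 7.1 condition? |
|---|---|---|
| Category up, dose unchanged | Yes (12.1.2) | Yes |
| Category up, dose raised | Yes (12.1.2) | No |
| CR maintained, dose raised | Yes (12.1.2) | Not an improvement, so not covered |
| Category up, dose cut | Yes (12.1.2 and 12.2.3) | Fails the improvement item as worded; meets the decrease item |
| Response lost, dose cut | Yes (12.2.3) | No |

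The response criteria do not close the gap. For PV, the 2009 ELN criteria restrict venesection but not drug dose. The IWG-MRT table in Appendix 6 has no cytoreductive-dose condition.

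**3. Direction relative to 7.1.** Patients who improve with an unchanged dose are a subset of those who improve or keep a CR. Patients with a dose decrease and no deterioration are a subset of those with a dose decrease. Each reported rate is therefore at least as high as the rate under the 7.1 condition.

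**4. Direction relative to a true tamoxifen effect.** This is not determined. A dose cut can lower the response category and hide an improvement. A dose increase takes the patient out of the cytoreduction count.

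**5. Illustration of size (assumed rates only).** Let m be the number of patients not in CR at baseline, a the share of them whose dose is raised, and b the share of those who then move up a category. Extra successes without a tamoxifen effect = m × a × b. Assume a from 10% to 30% and b from 30% to 50%, so that a × b runs from 0.03 to 0.15:
- m = 42 (nobody in CR at entry, the upper limit): 42 × 0.03 = 1.3 to 42 × 0.15 = 6.3 patients
- m = 21 (half in CR at entry): 21 × 0.03 = 0.6 to 21 × 0.15 = 3.2 patients

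The protocol gives none of m, a or b. Patients in CR at entry cannot move up, but they can be kept in CR by a dose increase, and this formula leaves them out.

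**The case against.** The strongest reply is that section 7.1 was never meant to define an endpoint. It is offered as guidance, with continuation encouraged and not mandated. It also uses a 25% allele-burden reduction where the primary outcome uses 50%, so it was not written to mirror the outcomes. This stands: a reader might infer that the plan breaks its own definition of benefit, and the text does not support that. What remains is that the authors recognised each signal could be produced by moving the background drug, and the outcomes do not carry that condition.

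A reader might also infer that reported benefit is biased upward overall. That is not shown. The excess is relative to the 7.1 conditions, and background changes can work against tamoxifen too.

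Other objections carry weight:
- One outcome is a descriptive secondary and the other is exploratory, with no decision attached to either.
- The word success is used only for the secondary outcome.
- No section describes raising hydroxycarbamide, though none forbids it. Entry criteria select patients with controlled disease, so increases may be few.
- Haematological response at weeks 12 and 24 is tabulated for patients who enter in response, so loss of response will be visible, but it is not linked to dose.

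These limit the weight of the point. They do not supply the missing handling of dose changes.

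**Conclusion.** The point holds as a weakness in the definition of two non-primary outcomes. Followed as written, the plan can credit tamoxifen with a category change, or a maintained CR, that a higher background dose produced. It can also count a dose cut that came with loss of response. The reported rates can only equal or exceed those under the 7.1 conditions. The excess cannot be sized from the protocol, and the range of about 1 to 6 patients in 42 rests wholly on assumed rates, at the upper limit of patients able to improve.

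A reader might extend this to the trial's conclusion on activity. That would be wrong: the conclusion rests on allele burden and the rule of 3 or more responders in 42, which this leaves untouched. The correction is worth making because it is cheap and the two percentages are hard to interpret without it.

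**What to change.** - **Sections 12.1.2 and 12.2.2 (and 2.2):** count improvement or maintained CR as success only if there has been no increase in cytoreductive dose and no new cytoreductive agent since baseline. State that this is deliberately a narrower restriction than the 7.1 wording, which excludes changes in either direction, so that improvement on a lower dose still counts.
- **Sections 12.1.3 and 12.2.3:** count a cytoreduction decrease only if the response (2009 ELN for ET/PV, IWG-MRT for MF) has not deteriorated from baseline.
- **Reporting:** show both outcomes in a joint table of category change by cytoreductive dose change. Put the excluded patients in a separate row, so that counts under the present definitions can be recovered.

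The cost is one derived flag and one table. Section 12.2.3 already needs cytoreductive dose at baseline and week 24, and response category is already assessed. The Concomitant Medication Form is completed continuously. Section 9.1 does not say that it records dose, so this should be confirmed if increases between those two time points are to be identified. Reported success rates may be slightly lower. The change concerns outcome definition only and alters no dosing rule.
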